## Abstract

**Introduction:**

Adiponectin and leptin play important roles in the central nervous system. During the postpartum period, there is a need for a better understanding of the relationship between these cytokines and the neurological development of the infant, as well as their influence on preventing maternal depressive symptoms.

**Objectives:**

To assess the correlation between adiponectin and leptin in maternal plasma and breast milk and their association with: infant neurodevelopment at 6 and 12 months of age; and maternal mental health over the first year postpartum.

**Methods:**

Prospective cohort study with four follow-up. Mothers and their newborns are recruited within the first 15 days postpartum (baseline). Follow-up visits occur at 2, 6, and 12 months postpartum. Visits include blood and breast milk collection, application of the Edinburgh Postnatal Depression Scale and Beck Depression Inventory to assess maternal mental health, application of the Bayley-III scale for infant developmental assessment, maternal and infant anthropometry and body composition, evaluation of reproductive history, mother-infant bonding, breastfeeding, consumption of ultra-processed foods, sleep quality, and socio-economic and demographic data.

**Results:**

The research received funds in August 2022, and participant recruitment began in September 2022. The sample size will consist of 95 mother-child pairs. As of September 2023, 68 participants have been recruited.

**Conclusion:**

The project will provide insights into the association between adiponectin and leptin with postpartum depression and infant neurodevelopment, ultimately promoting improved care and quality of life for these groups. Additionally, it will provide data on the type of delivery, infant physical growth, maternal and infant body composition changes, sleep quality, consumption of ultra-processed foods, and maternal metabolic health, including vitamin D metabolites, oxidized polyunsaturated fatty acid metabolites, phospholipid species and triacylglycerols, which are of significant relevance to public health and, when interconnected, may yield important results and contribute to the existing literature.

**Trial registration:**

**Name of the registry:** Brazilian Clinical Trials Registry (ReBec).

**Registration number:**
RBR-9hcby8c.

## Introduction

Human milk contains various nutrients, cytokines, peptides, enzymes, cells, immunoglobulins, proteins, and steroids capable of meeting the needs of the infant [1–3]. Some of these compounds are synthesized by the mammary glands, while others are taken from the maternal plasma. Maternal nutritional status, supplement usage, and dietary intake are some of the factors that can modify the plasma concentrations of these compounds and, consequently, the composition of the milk [4–7].

Among the cytokines already identified in breast milk are adiponectin and leptin, also known as biomarkers related to obesity or adipokines, as they are secreted by adipose cells [8]. It is believed that these cytokines found in breast milk have hormonal activities in various tissues of the neonate, especially when their own endocrine system is not fully functional, playing roles in energy metabolism and the regulation of body composition [9].

Additionally, studies suggest that adipokines may have activities in the brain, such as stimulating the genesis and neuronal excitability of the hippocampus, contributing to functions like learning and memory [10–14]. In recent years, the association between adipokines and cognitive function has been studied in other population groups, such as adults and the elderly [15–17]. More recently, some studies have provided data on the pediatric population.

In a cross-sectional study involving 50 participants conducted in Brazil, plasma concentrations of leptin were found to be inversely associated with cognitive development in children aged 6 to 24 months [18]. Using data from two cohorts of pregnant women in the United States and Canada, Li et al. (2019) found an association between adiponectin in umbilical cord blood and the intelligence quotient and memory in children at 3, 5, and 8 years of age [19]. However, to date, no studies have been found that investigate the association of maternal adipokines with the neurodevelopment of infants during the first year of life.

The period during which brain growth reaches its highest speed and exhibits the greatest plasticity occurs in the last trimester of pregnancy and the first two years of life. Therefore, the first one thousand days of life, from conception to 2 years of age, are recognized as crucial in the development trajectory, determining future health status, and being linked to increased cognitive and learning abilities throughout adulthood [20–22]. Hence, the identification of factors that may be associated with neurodevelopment in the first year of life, considered a window of opportunity for interventions, is of great significance in contributing to the health and quality of life of the population.

Regarding maternal outcomes associated with adipokine concentrations in postpartum women, further clarification is needed, particularly concerning mental health. The literature provides evidence that individuals with conditions such as depression and anxiety may have altered plasma concentrations of adipokines [23–25]. However, data regarding the relationship between adipokines and mental health during the postpartum period are limited and inconclusive [26].

Postpartum depression is particularly problematic because it not only impacts the health of the woman but also has a negative effect on the child’s health and complicates the use of medication due to the transmission of the drug to the infant through breast milk [27–30]. Mothers with postpartum depression often experience compromised physical health and engage in high-risk behaviors, such as alcohol and substance abuse. These women are less likely to adequately care for their own needs, as well as those of their children, and they may exhibit greater resistance to seeking and receiving postnatal care or adhering to medical prescriptions [31]. Moreover, suicide, with depression as its primary risk factor, stands as the foremost cause of maternal mortality in developed nations [32].

The role of adipokines in the central nervous system has been the focus of numerous studies over the last decade. In vitro studies demonstrate the role of adiponectin and leptin in stimulating neurogenesis, regulating the proliferation of hippocampal cells in a time- and dose-dependent manner [33,34]. Hence, the promotion of neurogenesis is a potential mechanism through which these adipokines can act on both stimulating infant neurodevelopment and inhibiting postpartum depressive symptoms. Additionally, adiponectin may indirectly influence depression through its actions on the hypothalamic-pituitary-adrenocortical axis (suppression of TNFα) and/or thyroid-mediated effects [13].

Given the scarcity of studies on this subject, the current project stands out for its potential innovation and ability to generate evidence that can assist in understanding and preventing developmental issues in childhood and throughout the life cycle. It also aims to contribute to the search for new strategies to prevent and treat postpartum depression.

In this way, the project seeks to clarify the relationship between adiponectin and leptin in maternal plasma and breast milk, maternal mental health, and infant neurodevelopment. This is based on the hypothesis that plasma concentrations of adiponectin and leptin are associated with the mental health of the breastfeeding mother and are correlated with the concentrations of these adipokines in breast milk. In turn, the consumption of milk with higher concentrations of adiponectin and lower leptin is expected to lead to greater neural stimulation in the infant, promoting better neurodevelopment.

In summary, the research questions to be responded to are: What is the relationship between maternal mental health and the concentrations of adiponectin and leptin in maternal plasma? How are the concentrations of adiponectin and leptin in maternal plasma related to their levels in breast milk? Does the consumption of breast milk with higher adiponectin and lower leptin concentrations result in improved neurodevelopmental outcomes in infants? What role do adiponectin and leptin play in the neurodevelopment of infants, particularly in the context of maternal mental health? These questions aim to dissect the intricate connections between maternal health, breast milk composition, and infant neurodevelopment, offering potential pathways for improving child health outcomes through targeted maternal support.

## Methods

To facilitate communication with research participants and reference to the project within the healthcare unit where the project takes place, the research title, "Adipokines in the plasma and milk of breastfeeding mothers in the first year postpartum: association with depressive symptoms and infant neurodevelopment," has been abbreviated to the acronym APPLE.

A prospective cohort study is being conducted at the National Institute of Women’s, Children’s, and Adolescents’ Health Fernandes Figueira (IFF), a healthcare unit affiliated with the Oswaldo Cruz Foundation (Fiocruz), located in Rio de Janeiro, Brazil. The IFF houses a maternity ward where approximately 1,000 deliveries occur annually. The cohort comprises four follow-ups: immediate postpartum (up to 15 days after delivery), the 2nd month postpartum, the 6th month postpartum, and the 12th month postpartum. Adult breastfeeding mothers and their children who are within the first 15 days postpartum are invited to participate in the study.

The recruitment of participants is being carried out through two approaches: (1) Project promotion for postpartum women who have given birth at IFF, followed by an active search for eligible patients who return for pediatric care at the Human Milk Bank (HMB) at IFF; (2) Promotion to personal contacts of the project team is conducted through messaging apps and social media platforms and interested individuals reach out via email or phone for eligibility assessment and scheduling of the initial evaluation.

The follow-up takes place at the HMB (milk collection), the pediatric service (infant development assessment), and the Nutrition and Metabolism Laboratory (body composition assessment, blood collection, and questionnaire administration). The specifics of the variables obtained at each follow-up wave of the study can be seen in **Fig 1**.

**Fig 1 pone.0310847.g001:**
[figure not shown]
Schedule of enrolment and assessments for the APPLE prospective cohort study.

To be included, breastfeeding mothers should be within 15 days postpartum, aged between 20 and 45 years, practicing exclusive breastfeeding (offering only breast milk, without tea or water, in the 5 days preceding entry into the study), residing in the city of Rio de Janeiro, having proficiency in the Portuguese language, and their newborn should have had an Apgar score of ≥ 7 at the fifth minute.

Breastfeeding mothers meeting the following criteria are ineligible for the study: those with chronic non-communicable diseases such as hypertension and diabetes (with the exception of obesity); individuals with infectious diseases like HIV and syphilis; those using antidepressants or other psychiatric medications; those who experienced a twin pregnancy; those with positive serology for Syphilis, Rubella, Toxoplasmosis, Cytomegalovirus, or Zika during pregnancy; and those who engaged in gestational surrogacy or temporary uterine cession ("surrogate mother"). Furthermore, puerperal women are ineligible if their newborns were preterm, exhibited any pathological conditions, had inappropriate weight for their gestational age, were diagnosed with conditions or malformations known to cause motor and cognitive deficits, or were admitted to a neonatal intensive care unit.

Regarding postpartum mothers who gave birth at IFF, their medical records are reviewed by trained professionals to assess eligibility for the study three times a week on alternate days, typically on Mondays, Wednesdays, and Fridays. On Fridays, assessments are conducted in the morning and early afternoon to minimize potential losses, considering that discharges from the maternity ward occur 2 or 3 days after delivery, depending on the type of delivery. Postpartum mothers identified as eligible through the medical record analysis are approached in the maternity unit for the initial project presentation. They receive a flyer with general information and contact details for the project, including phone and email.

In this scenario, the first meeting takes place on the pediatric evaluation date, which is a scheduled appointment at the Human Milk Bank (BLH) of IFF, at the time of maternity discharge, by the pediatric team. Between one and two days before the scheduled date, the project team contacts the postpartum mother to confirm her attendance at the appointment or reschedule it, aiming to prevent any losses due to forgetfulness or an inability to attend the originally scheduled date.

For postpartum mothers outside the IFF, promotion is being conducted among the team’s contacts through messaging apps and social media. Our outreach encourages interested pregnant individuals to register via an online form to assess eligibility and the expected delivery date. Closer to the expected delivery date, we contact the pregnant individuals to confirm their interest and schedule their participation. A new eligibility check is done by phone one day before the scheduled date to prevent unnecessary travel. If a woman has already given birth when she receives the promotion, we encourage her to contact a team member directly by phone, where eligibility criteria are assessed, and the evaluation is scheduled.

At the end of each assessment, postpartum mothers are scheduled for the next follow-up. To minimize follow-up losses, all participants are contacted via messaging apps or phone for confirmation or rescheduling. Another strategy to increase adherence includes sending a monthly image congratulating them on another month of their baby’s life on the baby’s birth date. This image also contains general information about the baby’s health during that period, such as developmental milestones, feeding, and vaccinations.

The participants started to be recruited in September 2022. Recruitment was open until the desired sample size is achieved (n = 117), which happened in July 2024. The follow-up will continue until all participants reach the one-year postpartum mark, projected to occur in July 2025.

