#### Maternal blood and breast milk samples (main exposure)

Human milk (a minimum of 10 ml and a maximum of 20 ml) is obtained using an electric breast pump. These samples are stored and transported under refrigeration within a maximum of 2 hours to the location for analysis. The samples are homogenized using a vortex (1 minute), divided into aliquots, and stored at -30°C for a maximum of 24 hours, after which they are moved to final storage at -80°C, where they remain until processing and analysis. Samples are collected at every follow-up visit or until the breastfeeding mother no longer has milk.

Blood samples are collected at visits T0, T2, and T3 in collection tubes containing EDTA. The samples are centrifuged (3500 rpm/15 minutes), and the plasma is separated into aliquots and stored in a freezer at -30°C for a maximum of 24 hours, after which they are transferred to final storage at -80°C, where they remain until processing and analysis. Commercial ELISA kits are used to determine the concentration of adiponectin and leptin in both breast milk and plasma.

In addition to adipocytokines, inflammatory biomarkers, including non-enzymatic oxidized metabolites of polyunsaturated fatty acids and species of phospholipids and triacylglycerols, as well as vitamin D metabolites, will be investigated. The oxidized metabolites and vitamin D metabolites will be analyzed through targeted lipidomics using a QTrap mass spectrometry platform (AB Sciex QTRAP 5500) [42], and lipid species through high-resolution semi-targeted lipidomics on an Orbitrap platform (Q-Exactive, Thermo-Finnigan) [43].

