### Data entry and statistical analysis

The collected data is being entered into the database using data entry masks specifically developed for the study in the RedCap software. Data storage and backup are provided by application and database servers located in the secure room of COGETIC/Fiocruz, with security levels in compliance with current legislation. A full backup is performed daily, and log backups are done hourly every day from 08:00 to 18:00.

The statistical analyses will be conducted using the Stata statistical software package [55]. Initially, data will be evaluated through a dispersion analysis. The normality of the data will be assessed using the Shapiro-Wilk test, and non-normally distributed variables will be subjected to a logarithmic transformation for subsequent analysis using parametric tests. Proportions of categorical variables will be compared using the chi-squared test, and differences between means of continuous variables will be tested with the Student’s t-test or ANOVA. Pearson’s correlation coefficient will be used to analyze the correlation between continuous variables, such as the correlation between adiponectin and leptin in plasma and milk.

The main variables (adiponectin and leptin concentrations, development scores, and depressive symptoms) will be treated as continuous. To assess the association between these variables, a longitudinal mixed-effects model (LME) will be used, adjusted for confounding factors. LME is a model capable of capturing changes within and between individuals, accommodating time-dependent and independent covariates, accounting for the correlation between repeated measurements in the same individual, and allowing for unbalanced time intervals. The total variance will be estimated by two components: the first measures the variance between individuals at the same time, and the second component measures the within-individual variance between each time point during follow-up. Postpartum time will be included as a fixed and random effect variable. If the response is described by a nonlinear function, a quadratic term will be included in the model.

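### T0 samples may come from any day up to day 15 postpartum, yet the plasma-milk correlation is unadjusted for sampling day, and a time term in the Bayley models would not adjust a T0 exposure

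*Protocol article*

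**What the plan says.** Methods describes the first wave as "immediate postpartum (up to 15 days after delivery", and the eligibility criteria repeat that "breastfeeding mothers should be within 15 days postpartum". Neither place gives a lower day limit. The feeding criterion is "practicing exclusive breastfeeding (offering only breast milk, without tea or water, in the 5 days preceding entry into the study".

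For women delivering at the study hospital, Methods says that "discharges from the maternity ward occur 2 or 3 days after delivery" and that "the first meeting takes place on the pediatric evaluation date". The postpartum day of that appointment is not given. Women recruited from outside attend on an arranged date.

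Under Maternal blood and breast milk samples, for milk: "Samples are collected at every follow-up visit or until the breastfeeding mother no longer has milk". For plasma: "Blood samples are collected at visits T0, T2, and T3". T0 is therefore one of three waves with both fluids.

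Under Data entry and statistical analysis: "Pearson’s correlation coefficient will be used to analyze the correlation between continuous variables, such as the correlation between adiponectin and leptin in plasma and milk". That section also plans a mixed model with postpartum time as a fixed and random effect, unequal intervals allowed, a quadratic term if needed, and adjustment for confounders chosen by a causal graph. It does not say whether time is coded in days or by wave.

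**The concern.** The plasma-milk relation is the first objective in the Abstract. At T0, two women may be sampled up to about two weeks apart in lactation. If concentrations change with day, part of the spread between women is a spread in sampling day, and a Pearson coefficient cannot separate the two.

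Bayley scores are measured at 6 and 12 months. A time term in that model describes the infant's age at assessment and leaves the timing of a T0 exposure unadjusted. At stake are a distorted T0 plasma-milk correlation and a diluted association wherever a T0 concentration predicts a later outcome, in a study whose Discussion already names small sample size as a limitation.

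**Working it through.** The plan has no figure of its own on this point, so there is nothing to reproduce. The check is a sensitivity calculation.

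**Inputs from the article:** T0 window to day 15; feeding look-back of 5 days; target of 117 pairs; Z = 1.96.

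**Assumptions, not in the article:** log concentration falls linearly with day, by a total of 30%, 50% or 70% over 15 days; sampling day is uniform; between-woman SD of log concentration is 0.5 to 0.7.

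**Formulas**
- Variance due to day, days 0-15: V = (ln(1 - fall))² / 12.
- Days 5-15 at the same daily slope: V × (10/15)² = 0.444 V.
- Share of T0 variance: V / (V + SD²).
- Factor on a correlation when drift affects one variable only: √(1 - share).
- Correlation produced by drift alone when the true value is zero and both fluids drift equally: +share if in the same direction, -share if in opposite directions.

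**Example:** 50% fall, SD 0.5. V = 0.693² / 12 = 0.0400. Share = 0.0400 / (0.0400 + 0.25) = 13.8%. Factor = √0.862 = 0.93.

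| Fall over 15 days | V, days 0-15 | Share, days 0-15 (SD 0.7 to 0.5) | Factor, days 0-15 | V, days 5-15 | Share, days 5-15 | Factor, days 5-15 |
|---|---|---|---|---|---|---|
| 30% | 0.0106 | 2.1-4.1% | 0.99-0.98 | 0.0047 | 1.0-1.8% | 1.00-0.99 |
| 50% | 0.0400 | 7.6-13.8% | 0.96-0.93 | 0.0178 | 3.5-6.6% | 0.98-0.97 |
| 70% | 0.1208 | 19.8-32.6% | 0.90-0.82 | 0.0537 | 9.9-17.7% | 0.95-0.91 |

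**Against the precision available at T0.** With 117 women, a correlation reaches two-sided 5% at about tanh(1.96/√114) = 0.18. Equal same-direction drift of 70% over days 0-15 would give an expected correlation of 0.20-0.33 from timing alone, which is above that threshold. The other rows, and every row for days 5-15, stay at or below it.

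**What the mixed model's time term removes.** A separate calculation took the adipokine as response at four waves, with an exponential early trend of assumed time constant. With time in exact days and a quadratic term, the T0 day variance remaining was 91% at a time constant of 5 days, 83% at 10, 54% at 30 and 13% at 90. With time coded by wave, all of it remains.

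**The case against.** The strongest reply is that the size rests on nothing in the article. No passage says that adiponectin or leptin changes materially in the first two weeks, and the scenarios run from trivial to substantial. That stands: the range shows what could happen, not what does.

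Four stronger readings are tempting and are not supported.

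- **That women enter on day 2 or 3.** Discharge falls then, but the study meeting is at a paediatric appointment booked at discharge, to which women return. Entry before day 5 is not established. If the feeding rule was applied literally, the window is about days 5-15, with 44% of the day variance. Nor is a difference in entry day between recruitment routes shown.
- **That none of the stated analyses deals with timing.** Where outcome and exposure share a visit, such as the Edinburgh scale and plasma at T0, postpartum time in exact days adjusts at least in part.
- **That T0 milk is the Bayley predictor.** The article does not say which wave's concentration is used, so this part is conditional. The Pearson point does not depend on it.
- **That the plasma-milk correlation must be inflated.** That needs drift in the same direction in both fluids. Opposite drift lowers it, and drift in one fluid attenuates it. Pairs at 6 and 12 months are unaffected by the T0 window.

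It can also be said that time coding and covariates belong to a fuller plan, and that the causal graph might select sampling day. That is fair for the mixed models and limits what can be asked there. It does not answer the Pearson analysis, which the article names without any adjustment.

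**Conclusion.** The point holds in a limited form. The article fixes a T0 window of up to 15 days and names an unadjusted correlation for the plasma-milk relation. If a T0 adipokine predicts Bayley scores, the model's time term does not represent the day of that sample. Under the assumptions above, sampling day is about 2-33% of T0 variance over days 0-15, or 1-18% if entry began at day 5. Only the largest assumed drift over the full window would by itself be expected to produce a nominally significant plasma-milk correlation. The direction of any bias is unknown. This is a nearly free improvement to the analysis; it does not show that the study's main results are invalid.

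**What to change.** 1. Compute the exact postpartum day of each T0 sample from the delivery and visit dates.
2. Report the T0 plasma-milk relation as a partial correlation on log concentrations, adjusted for sampling day.
3. Include T0 sampling day as a covariate wherever a T0 adipokine predicts a later outcome.
4. Code postpartum time in exact days in the mixed models. Because one curve over 12 months may fit a steep early change poorly, this does not replace steps 2 and 3.
5. If any women were sampled before day 5, repeat the T0 analyses on samples from day 5 onward. If none were, this step excludes nobody and can be dropped.
6. When reporting, state how the 5-day feeding rule was applied to any woman entered before day 5. Rewording the criterion now would change nothing, since recruitment closed in July 2024.

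The cost is one degree of freedom per analysis and no new data. For the partial correlation with 117 women, the standard error on the Fisher scale goes from 1/√114 = 0.0937 to 1/√113 = 0.0941.
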